## Abstract

**Background:**

Currently, there is no consensus regarding iron supplementation dose that is most beneficial for maternal and offspring health during gestation. Recommended iron supplementation dose does not preempt anemia in around 20% of the pregnancies, nor the risk of hemoconcentration in 15%. This deficit, or excess, of iron prejudices the mother-child wellbeing. Therefore the aims of the study are to determine the highest level of effectiveness of iron supplementation adapted to hemoglobin (Hb) levels in early pregnancy, which would be optimum for mother-child health.

**Methods/Design:**

*Design*: Randomized Clinical Trial (RCT) triple-blinded

*Setting*: 10 Primary Care Centers from Catalunya (Spain)

*Study subjects*: 878 non-anemic pregnant women at early gestation stage, and their subsequent newborns

*Methods*: The study is structured as a RCT with 2 strata, depending on the Hb levels before week 12 of gestation. Stratum #1: If Hb from 110 to 130 g/L, randomly assigned at week 12 to receive iron supplement of 40 or 80 mg/d. Stratum #2: If Hb >130 g/L, randomly assigned at week 12 to receive iron supplement of 40 or 20 mg/d.

*Measurements*: In the mother: socio-economic data, clinical history, food item frequency, lifestyle and emotional state, and adherence to iron supplement prescription. Biochemical measurements include: Hb, serum ferritin, C reactive protein, cortisol, and alterations in the HFE gene (C282Y, H63D). In children: ultrasound fetal biometry, anthropometric measurements, and temperament development.

Statistical analyses, using the SPSS program for Windows, will include bivariate and multivariate analyses adjusted for variables associated with the relationship under study.

**Discussion:**

Should conclusive outcomes be reached, the study would indicate the optimal iron supplementation dose required to promote maternal and infant health. These results would contribute towards developing guidelines for good clinical practice.

**Trial registration:**

This clinical trial is registered at http://www.clinicaltrialsregister.eu as EudraCT number 2012-005480-28

## Background

### Background and rationale

The prevalence of anemia during pregnancy is high (25%), even in economically developed industrialized countries [1-3]. Also, there is a frequent risk of hemoconcentrations in about 15% of pregnancies [2,4,5].

Ferropenic anemia during pregnancy has been related to an increase in risk of low birth weight of the newborn, premature birth, or less cognitive development of the child [1,5-8].

On the other hand, hemoconcentration, defined in a recent Cochrane review as values of hemoglobin >130 g/L at the 2nd trimester of gestation [4], has been associated with prejudicial effects in the mother and fetus. These include preeclampsia and oxidative stress in the mother [9], as well as an increase in premature birth, low birth weight, and small-for-gestational-age [7,10,11] of the fetus.

Also, low birth weight and general poor neonatal health have also been associated with environmental factors such as tobacco consumption, toxic environment, low socio-economic status, and prenatal psychological status of the mother e.g. high levels of anxiety [12,13]. These factors, and others related to the process of iron supplementation and the effects on mother and child, need to be controlled in studies investigating iron levels and pregnancy.

Prophylactic iron supplements are prescribed to avoid iron deficiency during pregnancy. The health authorities of Spain recommend an iron supplementation of 30 mg/d for non-anemic pregnant women [14]. However, since this dose is not currently marketed, obstetricians recommend a dose of around 40 mg/d of iron.

However, there is still no consensus on the best dose, nor schedule of iron supplementation, to prevent its deficiency during pregnancy, without provoking hemoconcentration [1,4,15].

The lack of evidence on the best pattern of iron supplementation could correspond to other factors, apart from the dietary intake of iron, such as iron status of the woman during the first trimester [6,16-18], or the presence of a genetic alteration that modifies the intestinal absorption of iron.

With respect to iron status during the first trimester, when gestation begins with low levels of iron, the percentage of women with deficit at the end of pregnancy is much greater [6,16,17]. On the other hand, high levels of hemoglobin at the start of pregnancy in women taking high dose supplements (>60 mg/d) increases the risk of hemoconcentration by the end of gestation [4,10,19].

With respect to genetic alterations, the presence of the C282Y and H63D polymorphisms in the HFE gene have been associated with higher levels of hemoglobin [10,20]; a situation that can be aggravated if the individual is prescribed daily supplements of iron.

These factors (initial iron status and genetic alternations together with dietary intake and iron supplements) can explain the presence of different subpopulations of pregnant women, all having different iron needs during pregnancy. As a consequence, a prescribed iron dose modified to the individual’s characteristics would be needed to obtain optimum benefit.

There have been some studies that evaluated the effect of different doses of iron on iron deficiency as a function of the woman’s initial hemoglobin concentration but none, to the best of our knowledge, have also take into account possible iron excess and adverse effects on the newborn.

Hemoglobin is an ideal parameter to classify the women as a function of iron status, due to the high correlation with the levels of serum ferritin and with the presence of genetic alterations in the HFE gene. These measurements are relatively easy and quick, and are already used systematically in standard clinical practice, and in pregnancy follow-up.

Our hypotheses are that:

1) In women without anemia at the start of the pregnancy, with normal hemoglobin values of between 110–130 g/L, an iron intake of 40 or 80 mg/d, depending on the initial serum ferritin levels and on the presence of genetic alterations in the HFE gene, would be more effective in preventing iron deficiency, without increasing the risk of hemoconcentration by the end of pregnancy. This would help optimize mother-child health status.

2) In women without anemia and with normal-high values of hemoglobin of >130 g/L, an iron intake of 20 or 40 mg/d, depending on the initial serum ferritin levels and on the presence of genetic alterations in the HFE gene, will be more effective in ameliorating the risk of hemoconcentration by the end of the pregnancy, without leading to iron deficiency.

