### Objective

The objective of the study is to determine the best grade of effectiveness (on mother-newborn health status), of an iron supplement adapted to the hemoglobin levels at the start of the pregnancy, relative to the usually-prescribed dose.

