### Sample size

The principal variables taken into account in calculating the size of sample needed are iron deficiency anemia, risk of hemoconcentration in the third trimester of pregnancy, and birth weight of the baby.

To achieve the study’s main objective, sample size is calculated in accordance with the following parameters: an alpha risk of 0.05 and a beta risk of 0.20 in a one-tailed test of comparison. A drop-out rate of 35% is factored-in.

To calculate the sample size needed to reduce the prevalence of iron deficiency anemia and hemocentration risk by 10 points, we consulted previous data from our research group [5,6,8]. We had observed a prevalence of 23.5% of iron deficiency anemia in the 3rd trimester in pregnant women with Hb levels of 110-130 g/L in the first trimester and a prevalence of risk of hemoconcentration of 14.7% in the 3rd trimester of pregnant women who started pregnancy with Hb levels of 130–150 g/L.

We found that, in Stratum #1 of the RCT, it will be necessary to include 283 women in each group and in Stratum #2 of the RCT 156 women would be necessary in each group.

With respect to child development, to detect differences in weight of the newborn ≥200 g taking into account a standard deviation (SD) of 450 g [5], the estimation suggests that it will be necessary to have 106 women in each group.

Hence, the overall study sample is calculated as 878 women: 566 in Stratum #1 and 312 in Stratum #2.

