#### Analysis of the primary outcome

The effects of iron dose supplement in each RCT on the biochemical iron status and mother-child health will be compared using regression models adjusted for those variables that can influence the relationship. Logistic regression or Cox models will be applied for qualitative variables such as, for example, the percentage of anemia or hemoconcentration at the end of pregnancy. Linear multiple regression models will be applied for dependent quantitative variables. The models will be adjusted for those variables that biologically affect the relationships studied, such as the serum ferritin levels, presence of alterations in the HFE gene, age of the mother, gestational age, parity, anthropometric indices, diet, and lifestyle, and the interactions between these variables. Initially included in the model will be all those variables that form part of the theoretical model and, in a second phase, the variables for entry into the model will be selected step by step (forward and backward) to achieve the most reduced stable models.

Conditions for the application of models will be verified using standard techniques that are based, essentially, on residuals analysis. The bilateral null hypothesis of normality, no difference, and non-significance of the regression coefficients, will be rejected when their probabilities are <5%. The data will be analyzed using the latest version of SPSS/PC package for Windows.

Data will be analyzed in 2 ways:

a) Intention-to-treat analysis

The principle of “intention-to-treat” is a way of analyzing the results that considers all individuals entered into the study, according to the group to which they were originally assigned, although they may not have complied with the protocol. In this case, in all the circumstances that have led to not having hemoglobin determinations before delivery, we will proceed to incorporate at this time-point the immediately-prior determination of hemoglobin. All randomized participants randomized who had received at least one dose of study medication will be included.

b) Per-protocol analysis

Included in the analysis will be only those pregnant women who received the allocated intervention at randomization. The per-protocol population (PP) will include those participants who had taken at least the 80% of the study medication, with proper assessment of adherence, or without any major protocol violations.

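### Both hypotheses make the better dose depend on ferritin and HFE status, but the objective and sample size address only the average dose difference, and any dose-by-biomarker term is left to stepwise selection

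*Protocol article*

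**What the plan says.** **Hypotheses (Background and rationale).** Hypothesis 1 (hemoglobin 110–130 g/L) names 40 or 80 mg/d as more effective. Hypothesis 2 (above 130 g/L) names 20 or 40 mg/d. These pairs are the two randomized arms of each stratum. Both hypotheses make the choice within the pair conditional: "depending on the initial serum ferritin levels and on the presence of genetic alterations in the HFE gene".

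**Objective.** The aim is the effectiveness "of an iron supplement adapted to the hemoglobin levels at the start of the pregnancy, relative to the usually-prescribed dose". Neither ferritin nor HFE appears.

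**Sample size.** Each stratum is sized to "reduce the prevalence of iron deficiency anemia and hemocentration risk by 10 points", starting from 23.5% iron deficiency anemia (Stratum 1) and 14.7% hemoconcentration risk (Stratum 2), both in the third trimester. No subgroup or interaction enters.

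**Analysis of the primary outcome.** "The models will be adjusted for those variables that biologically affect the relationships studied, such as the serum ferritin levels". HFE status, age, parity and other covariates follow, and the list ends with "diet, and lifestyle, and the interactions between these variables". After an initial full model, "the variables for entry into the model will be selected step by step (forward and backward) to achieve the most reduced stable models".

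**The concern.** If the better dose differs with ferritin or HFE status, the quantity that answers the hypothesis is the difference in dose effect between biomarker groups. The plan fixes no such quantity. The list to which the phrase about interactions refers does not contain dose, and whatever interactions are meant go through data-driven selection.

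Two errors could follow. A real dose-by-biomarker effect could be removed because the trial has little power for it, and its absence from the final model read as evidence that one dose suits everyone. Or a chance interaction could survive selection and be presented as confirming the hypothesis, with an estimate and p-value that ignore the selection. Either would bear on the trial's stated motive, which is adapting the supplement to the individual woman.

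**Working it through.** **1. What the planned numbers were sized for.** Inputs from the Sample size section: one-tailed alpha 0.05, power 0.80, drop-out 35%, a 10-point reduction. Arcsine formula: n = 2(1.645 + 0.842)² / h², with h = 2·asin√p1 − 2·asin√p2.

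- Stratum 1: 0.235 to 0.135, h = 0.2597, n = 183.3. Rounded up, 184/0.65 = 283.1; the plan states 283.
- Stratum 2: 0.147 to 0.047, h = 0.3499, n = 101.0. 101.0/0.65 = 155.4, rounded up to 156; the plan states 156.

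Both figures are reproduced by the average dose comparison alone.

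**2. Evaluable women per arm.** 283 × 0.65 = 183.95 and 156 × 0.65 = 101.4.

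**3. Precision of an interaction.** Take a binary modifier present in a share f of women in both arms. With similar variances in the two biomarker groups, the standard error of the difference between two risk differences is the standard error of the dose effect times 1/√(f(1−f)):

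- f = 50%: 2.00
- f = 30%: 2.18
- f = 10%: 3.33

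The variance sum p1(1−p1) + p2(1−p2) is 0.1798 + 0.1168 = 0.2966 in Stratum 1 and 0.1254 + 0.0448 = 0.1702 in Stratum 2. The standard error of the dose effect is √(0.2966/183.95) = 0.0402 and √(0.1702/101.4) = 0.0410.

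**4. Two-sided power, Φ(δ/SE − 1.96).** The Statistical methods section tests bilaterally at 5%, so two-sided power is the relevant figure. Three cases:

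- *A*: interaction δ = 10 points, variances as in step 3.
- *B*: dose effect 10 points in the group with share 1−f and 0 in the group with share f. SE² = [(p1(1−p1) + p2(1−p2))/(1−f) + 2·p1(1−p1)/f]/n.
- *C*: full reversal, 10 points better in one group and 10 points worse in the other, so δ = 20 points.

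| Stratum | f | A | B | C |
|---|---|---|---|---|
| 1 | 50% | 24% | 22% | 70% |
| 1 | 30% | 21% | 19% | 63% |
| 1 | 10% | 11% | 10% | 32% |
| 2 | 50% | 23% | 19% | 69% |
| 2 | 30% | 20% | 16% | 61% |
| 2 | 10% | 11% | 9% | 31% |

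Example (Stratum 1, A, f = 50%): SE = 2.00 × 0.0402 = 0.0803; 0.10/0.0803 − 1.96 = −0.715; Φ = 0.24.

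One-sided at 5%, case B gives 17% to 32% in Stratum 1 and 15% to 29% in Stratum 2. Case C gives 44% to 80% and 43% to 79%. Only a complete reversal with a nearly even split comes near 80%, and only one-sided.

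**5. Numbers that case B would need.** For 80% one-sided power, randomized per arm: 1249 (f = 50%) to 3734 (f = 10%) in Stratum 1, against 283 planned; 801 to 2566 in Stratum 2, against 156.

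**The case against.** - **The text can be read more generously.** The interactions mentioned might be meant to include dose, and the first-phase model is to contain everything in the theoretical model, in which ferritin and HFE play a part. This stands: a reader might infer that the biomarker hypotheses cannot be tested at all under the plan, and the wording does not support that. But even on the generous reading no dose-by-biomarker term is named, and the second phase still exposes one to selection.
- **The average dose effect is the declared target.** Objective, stratified design, the 40 mg/d reference and sample size agree on it, and hemoglobin is justified as a stratifier by its correlation with ferritin and HFE status. This stands. The average comparison is planned and sized; the mismatch lies with the hypotheses.
- **The hypotheses can be contradicted.** Because both arms are named, a reader might infer that any result would agree with them. Each hypothesis carries a second condition (no added hemoconcentration risk; no resulting iron deficiency), so that goes too far. What is missing is a fixed direction for the dose comparison.
- **The wording suggests a reversal, which has more power.** True, and case C shows it. It still reaches at most 70% two-sided.
- **No selection threshold is given.** Correct. The 5% in that section is the rule for rejecting null hypotheses, so no particular p-value for dropping a term can be assumed.
- **Interaction terms and coding belong in an analysis plan, and few trials power interactions.** Fair, and their absence alone would be no finding. Here, though, the article states the selection rule itself, and that rule sits badly with its own hypotheses.

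**Conclusion.** The point holds as a mismatch between the hypotheses and the rest of the plan. The hypotheses assert effect modification by ferritin and HFE; the objective and sample size address the average dose difference within each hemoglobin stratum; and the modelling rule leaves any dose-by-biomarker term unnamed and open to stepwise removal or chance retention. It does not undermine the average comparison, which the trial plans and sizes.

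Two-sided power is about 9% to 24% for a 10-point interaction and about 31% to 70% for a full reversal, across both strata. These figures assume a binary modifier with a share of 10% to 50%, the interaction sizes shown, effects measured as risk differences, and 65% of randomized women evaluable. The documents give no carrier share, ferritin cut-off or interaction size. The figures do not carry over directly to ferritin analysed as a continuous variable or to an interaction on the odds-ratio scale.

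**What to change.** 1. State the confirmatory hypothesis in each stratum as the between-dose difference in the outcome that sized it: third-trimester iron deficiency anemia in Stratum 1 and third-trimester hemoconcentration risk in Stratum 2.
2. Pre-specify a secondary model in each stratum with dose × baseline ferritin (continuous) and dose × HFE carrier status, with carrier status defined in advance. Keep the dose, biomarker and interaction terms in that model whatever the data show, exempt from forward and backward selection.
3. Report both interactions with 95% confidence intervals, label them exploratory, and do not read a non-significant interaction as absence of effect modification.

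The cost is wording in the protocol and analysis plan. Ferritin and HFE genotype are already to be measured, and neither the sample size nor the treatments change. The downside is that the claim that the better dose depends on ferritin or HFE becomes exploratory.

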### Objective

The objective of the study is to determine the best grade of effectiveness (on mother-newborn health status), of an iron supplement adapted to the hemoglobin levels at the start of the pregnancy, relative to the usually-prescribed dose.

## Methods

### Trial design

Multi-centered, parallel groups, controlled, triple blind, randomized clinical trial (RCT) subdivided in 2 strata as a function of the hemoglobin (Hb) levels at the start of the pregnancy:

– Stratum #1: If the levels of Hb are situated between 110 and 130 g/L, the individual will be randomly assigned to an iron dose supplement of 40 or 80 mg/d

– Stratum #2: If the levels of Hb are >130 g/L, the individual will be randomly assigned to an iron dose supplement of 40 or 20 mg/d

The overall design of the study is summarized in Figure 1. This trial has been registered with EU Clinical Trials Register, EUCTR-2012-005480-28.

**Figure 1 F1:**
[figure not shown]
Study design.

### Methods: participants, interventions, and outcomes

#### Study setting

The study will be conducted in 10 Primary Care Centers (PCC) of the Catalunya Sexual and Reproductive Health-care Service [*Atención a la Salud Sexual y Reproductiva (ASSIR)*] of the Catalan Institute of Health [*Instituto Catalán de la Salud (ICS)*]. These Centers provide care for 3,500 potential pregnancies per year. The specialist health-care workers include gynecologists and midwives. The participating reproductive health-care services (RHS) provide cover for urban, suburban, and rural PCCs.

### Eligibility criteria

The participants will need to fulfill the following inclusion, and none of the exclusion, criteria.

– Inclusion criteria: Adult female older than 18 years of age with ≤ 12 weeks gestation without anemia (Hb >110 g/L), capable of understanding the official State languages (Castilian or Catalan), who can understand the characteristics of the study, and who sign the informed consent form.

– Exclusion criteria: Multiple pregnancy, taking >10 mg iron during the months prior to week 12, hypersensitivity to egg protein (due to the iron prescription formula contains ovalbumin), previous serious illness (immunosuppressed status) or chronic illness that could affect the nutritional development (e.g. cancer, diabetes), malabsorption, and liver disease such as chronic hepatitis or cirrhosis. The risk factors of pregnancy to be considered as exclusion criteria are: adverse obstetric history, previous uterine surgery, heart disease grade 2, 3 or 4, endocrinopathy, suspected fetal malformation, morbid obesity, preeclampsia, maternal infection, uterine malformation, perinatal recurrent death, alcoholism, diabetes 1 and 2, uterine cervical incompetence.

### Interventions

The clinical follow-up of the pregnancy in the PCC will be according to the program set by RHS. This includes a clinical visit at recruitment into the present study, a visit every trimester, and one at 40 days post-partum (Figure 1).

In the recruitment visit before week 12 of the pregnancy, the inclusion criteria will be assessed (except the Hb levels and the number of fetuses) as well as the exclusion criteria. Informed consent will be solicited. A clinical history will be recorded, as will a questionnaire regarding the ingestion of iron supplements, multi-vitamins, or other treatments (Drugs_Q) and, if a smoker, the Fagerstrom test for tobacco dependency. A blood sample for standard biochemical analyses (including hemoglobin) will be sent for processing in the centralized laboratory.

At visit 1, around the 12th week of gestation, Hb levels will be evaluated as will be the number of fetuses (using echography) to confirm that the inclusion criteria are fulfilled. If fulfilled, the individuals will be retained in the study and, if not, will be transferred out of the study, and considered a screening failure. The remaining women will be assigned to Stratum #1 or Stratum #2 of the study and will be randomized with respect to iron supplement prescription. Clinical history will be taken, including the use of multi-vitamins and iron supplements (on the questionnaire abbreviated as “Drugs_Q”) and the following questionnaires filled-in: Food Frequency Questionnaire (FFQ); International Physical Activity Questionnaire (IPAQ); State-Trait of Anxiety Inventory (STAI) and the Fagerstrom questionnaire (Fagerstrom_Q). The ultrasound data on the fetus will be recorded. Venous blood will be taken for analyses, the results of which will be reviewed in the next clinical visit. The iron supplementation that will be needed at the next visit will be prepared for distribution. Adverse events occurring since the previous visit will be recorded.

At visit 2, around week 24 of gestation, clinical history will be taken, and will include the Drugs_Q, which, from this visit onwards, includes the adherence to the iron supplementation prescribed. The following questionnaires are filled-in: FFQ; IPAQ; STAI, Fagerstrom_Q. The fetal ultrasound data will be registered. The biochemical analyses/results will be reviewed and a further blood sample taken for analysis, the results of which will be reviewed at the next clinical visit. The iron supplementation that will be needed at the next visit will be prepared for distribution. Adverse events occurring since the previous visit will be recorded.

At visit 3, around week 36 of gestation, the clinical history will be taken, the Drugs_Q as well as the FFQ; IPAQ; STAI, Fagerstrom_Q questionnaires will be filled-in. The fetal ultrasound data will be recorded and the biochemical results will be evaluated. A further blood sample will be taken for analyses, the results of which will be discussed at the next clinical visit.

The iron supplementation that will be needed at the next visit will be prepared for distribution. Adverse events occurring since the previous visit will be recorded.

At visit 4 (40 days post-partum), the clinical history will be taken, the Drugs_Q and the FFQ; IPAQ; STAI; Fagerstrom_Q questionnaires will be filled-in. A questionnaire on post-partum depression (Edinburgh Postnatal Depression Scale; EPDS) and the Parenting Stress Index (PSI) will be applied. The standard laboratory analyses results will be discussed. A further blood sample will be taken for analyses. Data on birth and the newborn will be recorded (weight and height). Clinical history of the baby will be recorded, including: anthropometric data (weight, height, head circumference) and cognitive development will be assessed (Bayley III), as well as behavioral and temperament (Early Infancy Temperament Questionnaire; EITQ). Adverse events occurring since the previous visit will be recorded.

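### The per-protocol rule is joined by *or* and, read literally, admits women with major violations; a smaller point is that the timing of two exclusion checks needs reconciling

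*Protocol article*

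**What the plan says.** **Per-protocol set.** Under Analysis of the primary outcome, item b first limits the per-protocol analysis to women who received the intervention allocated to them. It then defines the population as "those participants who had taken at least the 80% of the study medication, with proper assessment of adherence, or without any major protocol violations". Women who become anemic after entry are removed from this set by a separate rule.

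**Eligibility.** The section Eligibility criteria opens with a general rule: "The participants will need to fulfill the following inclusion, and none of the exclusion, criteria". Among the exclusions are "taking >10 mg iron during the months prior to week 12" and a suspicion of fetal malformation.

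**When eligibility is judged.** Interventions describes two steps.

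- At the recruitment visit, before week 12, "the inclusion criteria will be assessed (except the Hb levels and the number of fetuses) as well as the exclusion criteria". Iron use is recorded there with "a questionnaire regarding the ingestion of iron supplements, multi-vitamins, or other treatments" (Drugs_Q).
- At visit 1, around week 12, "Hb levels will be evaluated as will be the number of fetuses (using echography) to confirm that the inclusion criteria are fulfilled". Women who fail this check become screening failures; the others are assigned to a stratum and randomized. The text then adds: "Clinical history will be taken, including the use of multi-vitamins and iron supplements". That is Drugs_Q again, and the ultrasound data are recorded at the same visit.

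**The concern.** A per-protocol set is meant to show what the assigned dose does in women who took it as planned. It can do so only if its conditions apply together. Joined by *or*, one condition can stand in for another, and a woman with a major violation can qualify on adherence alone. Non-study iron makes this concrete. Drugs_Q records it at every visit, but the article does not say how it counts for this set, and the 80% rule looks only at study medication.

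The timing point is smaller. The iron exclusion covers a window that closes at week 12, so it cannot be settled finally at a visit held before then. A suspicion of fetal malformation will often depend on an ultrasound, and the article first describes one at visit 1. The article names what is held over to visit 1, and neither criterion is on that list. The data needed to apply both are collected at visit 1, but no sentence ties them to a decision on retention.

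**Working it through.** **1. The per-protocol rule.** Let A = took at least 80% of study medication, B = adherence properly assessed, C = no major protocol violation. The evident intention is A and B and C. The printed sentence can be parsed as A and (B or C), or as (A and B) or C.

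| A | B | C | A and B and C | A and (B or C) | (A and B) or C |
|---|---|---|---|---|---|
| yes | yes | yes | in | in | in |
| yes | yes | no | out | in | in |
| yes | no | yes | out | in | in |
| yes | no | no | out | out | out |
| no | yes | yes | out | out | in |
| no | yes | no | out | out | out |
| no | no | yes | out | out | in |
| no | no | no | out | out | out |
| **Combinations admitted** | | | **1** | **3** | **5** |

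Some rows may be empty in practice; for instance, intake below 80% may itself be classed as a major violation. The second row does not depend on the parse: an adherent woman with a major violation is in the set under both.

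**2. The timing of the exclusions.**

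| Item | Information available at | Judged at, as written |
|---|---|---|
| Hb | visit 1 | visit 1 |
| Number of fetuses | visit 1 (ultrasound) | visit 1 |
| Iron above 10 mg before week 12 | complete only at about week 12; Drugs_Q at visit 1 | recruitment visit |
| Suspected fetal malformation | first ultrasound described at visit 1, with prenatal diagnostics (The fetus) | recruitment visit |

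The first two rows are consistent. In the last two, the judgement is placed before the information is complete.

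**3. The dose contrast.** The plan's own figure for Stratum #2 (Trial design) is 40 − 20 = 20 mg/d. If women in both arms take a further x mg/d of non-study iron, the contrast is (40 + x) − (20 + x) = 20 mg/d.

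The article gives no value for x or for the share f of women concerned. As assumptions only, take x = 20 to 30 mg/d and f = 10% to 30%, equal in both arms.

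- Among users, the lower arm receives 20 + 20 = 40 to 20 + 30 = 50 mg/d, and the upper arm 60 to 70 mg/d. The difference stays at 20. The ratio falls from 40/20 = 2.0 to 60/40 = 1.5 or 70/50 = 1.4.
- Averaged over an arm, the shift is f × x, from 0.10 × 20 = 2 to 0.30 × 30 = 9 mg/d in each arm. The means are 22 to 29 and 42 to 49 mg/d, again 20 apart.

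The absolute contrast therefore stands, while the doses such women actually receive differ from those assigned.

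**The case against.** The strongest reply on timing is that the general rule in Eligibility criteria governs: a woman found at visit 1 to have taken iron above the limit meets an exclusion and is ineligible, whatever the visit schedule says. The visit 1 sentence should also not be read too literally. Multiple pregnancy is listed as an exclusion, yet Interventions checks the number of fetuses "to confirm that the inclusion criteria are fulfilled", so the article uses that phrase loosely for eligibility in general. The order of steps within a visit is commonly left to the full protocol. All of this stands. It reduces the timing point to a mismatch in wording.

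A reader might infer that women who start iron between the two visits are randomized, and that this blurs the 20 mg/d contrast in Stratum #2. The documents do not support either step. No sentence says that such women are kept. Iron taken before randomization is a baseline feature, balanced in expectation because allocation is random and separate within each stratum, and equal additional intake leaves the absolute contrast unchanged. To compare a supplemented woman in the 20 mg arm with an unsupplemented woman in the 40 mg arm is to compare unlike women. A smaller effect would need a dose response that flattens at higher intake, and the article gives no figure for one.

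On the per-protocol rule, it can be said that the *or* is only loose wording in a secondary analysis, and that the list of major violations, which may already include non-study iron or ineligible entry, belongs in the analysis plan. The absence of that list is indeed no fault. But a list of violations excludes nobody who can qualify through the other branch of an *or*, so this part of the objection does not remove the error.

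**Conclusion.** The per-protocol definition is wrong as printed. Under either parse it admits adherent women with major violations, and under one parse also women below 80% intake. How many women this concerns cannot be derived from the article, because it gives no expected rate of violations or of non-study iron use.

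The mismatch between Eligibility criteria and Interventions is real but minor. It rests on the visit schedule as written, and the full protocol may already resolve it.

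Neither point biases the intention-to-treat comparison, and the assigned contrast remains 20 mg/d. At most, some ineligible women dilute the population being tested, and the per-protocol set does not reflect the assigned dose. The 20 to 30 mg/d and the 10% to 30% used above are assumptions without a source in the article, and the conclusion does not depend on them.

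**What to change.** 1. In the per-protocol definition, replace *or* with *and*, so that intake of at least 80%, proper assessment of adherence and absence of major violations are all required.
2. State, there or by reference to the analysis plan, how non-study iron recorded on Drugs_Q counts for the per-protocol set.
3. Reconcile Eligibility criteria with Interventions: say that the Drugs_Q and ultrasound already done at visit 1 are applied to the existing iron and fetal-malformation exclusions before randomization, and that women who meet them are screening failures.

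The criteria themselves and the intention-to-treat set do not change, and no new assessment is needed. The cost is an edit to the text, slightly more screening failures and a slightly smaller per-protocol set.
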